### Sample size estimation

The NDI and the NPRS are the independent primary outcome measures and sample size estimates were carried out for both outcome measures. An MCID for the NDI of 7 has been determined for cervical radiculopathy [48]. Using a reported NDI SD of 9.2 [48] for this patient group, with a two-sided 5% significance level and a power of 80%, a sample size of 29 participants per group is necessary. An MCID for the NPRS of 2 has been determined for mechanical neck pain, including cervical radiculopathy [43] and a SD of 1.85 [48]. Using these figures, with a two-sided 5% significance level and a power of 80%, a sample size of 15 per group was calculated. An online sample size calculator [49] for comparing means of 2 independent groups, that utilises reference tables [50] was used. The larger sample size per group calculated using the NDI was chosen and an additional 10% was added to account for anticipated dropout. In total, a sample size of 64 participants will be recruited.

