### Data analysis plan

Baseline demographic characteristics and all outcome measures will be described and analysed using SPSS (IBM, version 24) or Stata statistical software (Statacorp LLC, Release 15). Descriptive characteristics will be presented for both groups following the CONSORT Statement. Data will be checked for normality using the Shapiro-Wilk test. Marginal effects will be used to calculate effect sizes for specified values for baseline differences. Results will be reported as mean differences between the groups and their 95% confidence intervals. Poisson regression will be used where data are non-parametric (Bland and Altman, 2011).

Statistical analysis will include two-way (treatment x time) ANOVAs and MANOVAs for between and within-group differences and interactions. Intention to treat analysis will be the primary approach employed. A per protocol analysis will also be undertaken and results compared to assess the impact of data that is not missing at random (NMAR) (Armijo-Olivo et al., 2009).

Secondary analysis will explore if any of the baseline outcome measures, symptom duration and group allocation are predictors of outcome (pain and disability) at 3 months. Appropriate multivariable regression analysis will be performed (linear or logistic).

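### Comparing per-protocol with intention-to-treat results cannot show the impact of data not missing at random, so that purpose should be removed and given to a delta-adjusted sensitivity analysis

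*Protocol article*

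**What the plan says.** Three statements in the Data analysis plan bear on this. The analysis set is fixed by "Intention to treat analysis will be the primary approach employed". The model is given by "Statistical analysis will include two-way (treatment x time) ANOVAs and MANOVAs for between and within-group differences and interactions". The role of the second analysis set is given by "A per protocol analysis will also be undertaken and results compared to assess the impact of data that is not missing at random (NMAR"), with a literature citation attached.

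The Sample size estimation section deals with dropout only through numbers: "an additional 10% was added to account for anticipated dropout".

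The article does not state how missing outcomes enter the ITT analysis, and it names no other method for data not missing at random (NMAR).

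**The concern.** NMAR is a statement about outcomes nobody recorded: participants who left would have scored differently from comparable participants who stayed. To assess its impact, an analysis has to vary what is assumed about those unseen scores. A per-protocol analysis does something else. It removes people who did not follow the allocated programme and analyses what was observed in the rest. The gap between the two results therefore carries the effect of selecting on adherence after randomisation.

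The sentence fixes how the comparison will be read, and that reading can fail both ways. Similar results would be taken as a sign that dropout was harmless, whatever the truth. Different results would be blamed on NMAR data when the cause may be adherence selection.

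The question matters in this trial. Under Randomisation, participants cannot be blinded; the primary outcomes are self-reported; and under Interventions, the control arm receives weekly phone contact and is offered treatment at 12 weeks to support retention.

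**Working it through.** **Inputs from the Sample size estimation section:** NDI target difference 7, SD 9.2, two-sided 5%, 80% power, 29 per group, 10% dropout, 64 in total. All shifts, dropout mechanisms and adherence rates below are assumptions.

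**Step 1. The plan's own figures reproduce.**
- NDI: the t-test calculation for 7/9.2 gives 28.1, so 29 per group, as in "with a two-sided 5% significance level and a power of 80%, a sample size of 29 participants per group is necessary".
- Pain scale (NPRS): 2/1.85 gives 14.5, so 15, as in "a sample size of 15 per group was calculated".
- Total: 58 × 1.10 = 63.8, so 64. The concern does not touch the sample size.

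**Step 2. Does the ITT/per-protocol gap track NMAR?** A simulation used 32 per arm, SD 9.2, a true difference of -7 (negative favours physiotherapy), 10% missing per arm and 20% non-adherence in the physiotherapy arm, over 20,000 runs. ITT was taken as all available outcomes. NMAR dropout meant that physiotherapy participants in the worst fifth of outcomes left with probability 0.5. Outcome-related non-adherence meant that those in the worst 40% were non-adherent with probability 0.5.

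| Dropout | Non-adherence | ITT | Per protocol | Gap |
|---|---|---|---|---|
| Completely at random | Unrelated to outcome | -6.98 | -6.99 | -0.01 |
| Completely at random | Related to outcome | -7.00 | -9.23 | -2.23 |
| NMAR | Unrelated to outcome | -8.44 | -8.44 | 0.00 |
| NMAR | Related to outcome | -8.44 | -10.24 | -1.80 |

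Row 2 is a false alarm: nothing is NMAR, yet the gap exceeds 2 points. Row 3 is false reassurance: ITT is biased by about 1.4 points and the gap is zero. In row 4 per protocol lies further from the truth than ITT.

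Hand check of row 3: the mean of the worst fifth is 9.2 × 0.280/0.2 = 12.9 above the arm mean. Losing 10% of the arm from that group moves the rest by -(0.10 × 12.9)/0.90 = -1.43, giving -8.43.

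Hand check of row 2: the mean of the worst 40% is 9.2 × 0.386/0.4 = 8.9 above. Excluding 20% of the arm moves the rest by -(0.20 × 8.9)/0.80 = -2.22, giving -9.22.

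**Step 3. Size of a one-arm departure.** Change in difference = missing fraction × mean shift.
- 0.10 × 5 = 0.5 points; 0.5/7 = 7%
- 0.10 × 10 = 1.0 point; 1.0/7 = 14%
- 0.10 × 15 = 1.5 points; 1.5/7 = 21%

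**Step 4. Where would a conclusion tip?** The standard error with 29 per group is 9.2 × √(2/29) = 2.42. With t = 2.00 on 56 degrees of freedom, the 95% half-width is 4.84.
- Observed difference 7: nearer limit 7 - 4.84 = 2.16; tipping shift 2.16/0.10 = about 22 points.
- Observed difference 5.5 (chosen for illustration): nearer limit 0.66; tipping shift 0.66/0.10 = about 7 points.

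These hold the standard error fixed. Multiple imputation would usually widen it a little and tip slightly earlier.

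**The case against.** **The article is condensed.** A fuller protocol or analysis plan may hold proper imputation and sensitivity analyses. That stands, and it limits the point. A reader might infer that the trial has no valid check on informative dropout at all; one condensed article cannot support that. An unseen document could add a valid method, but it could not make this sentence correct.

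**ITT may not be complete-case.** A reader might infer from the ANOVA and MANOVA wording that dropouts are absent from both analysis sets. The article does not say so: a long-format ANOVA with a subject term can keep participants with some visits, and imputation is not excluded. This also qualifies the simulation, since the zero gap in row 3 rests on available-case ITT and on adherence unrelated to outcome. The conclusion survives, however. If ITT imputes and per protocol does not, the gap mixes imputation with adherence selection and still does not isolate NMAR.

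**Dropout may be small and benign.** The primary endpoint is early, at 4 weeks, controls have an incentive to stay, and the Discussion reports acceptable retention in the internal pilot. These points lower the likely size of the problem. The pilot was a 10% sample, about 6 of 64 people, so it cannot rule out informative loss.

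**The effect is modest.** A 22-point shift is 22/9.2 = 2.4 planning SDs, so a full 7-point result would be robust in that reference case. That is fair. The result is not known in advance, and the planned comparison could not tell a robust result from a fragile one.

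**Conclusion.** The point holds as an error in a stated purpose. The per-protocol comparison cannot assess the impact of NMAR data, and reading it that way can reassure falsely or alarm falsely. The ITT primary estimate is unaffected, and the per-protocol analysis remains legitimate as an adherence analysis.

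The size is moderate. One-arm shifts of 5 to 15 NDI points at 10% dropout are worth 0.5 to 1.5 points against a target of 7 and a half-width of 4.84. This would not overturn an observed 7-point difference but could overturn one near 5.5. The target, SD and dropout rate are the protocol's; the shifts and the simulated mechanisms are assumptions.

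A reader might also infer that the ANOVA and MANOVA must give way to another primary model. Correcting this error does not require that.

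**What to change.** 1. Delete the NMAR purpose from the per-protocol sentence and describe that analysis as a supplementary adherence analysis.
2. Add an NMAR sensitivity analysis for the 4-week NDI and NPRS. Impute missing outcomes for all randomised participants by multiple imputation under missing at random, then add a delta to the imputed values, in each arm separately.
3. Increase the delta until the conclusion changes, and report that tipping point, or stop at the limit of the scale. A fixed grid ending at 15 NDI points would miss the 22-point tipping case shown above.

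The cost is a revised sentence and a few hours of analysis work. No new data, change in sample size or change in trial conduct is needed.

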## Discussion

An internal pilot feasibility study of 10% sample has explored the initial recruitment strategy and retention rates of the study, in alignment with MRC Guidelines (MRC, 2008). Retention strategies proved acceptable but recruitment strategies were insufficient, leading to geographical trial expansion and the addition of self-referral through social media advertising. This trial of non-provocative multimodal physiotherapy for recent onset CR, will elucidate whether physiotherapy actively improves the pain and disability associated with the condition, when compared with advice only.

## Data Availability

Not applicable.

## Abbreviations

CPR: Clinical prediction rule
CR: Cervical Radiculopathy
CROM: Cervical range of motion
CSM: Cervical Spondylotic Myelopathy
FABQ: Fear Avoidance Belief Questionnaire
GROC: Global Rating of Change Scale
HADS: Hospital Anxiety and Depression Scale
ICC: Intraclass correlation coefficient
MCID: Minimal clinically important difference
MP: Multimodal physiotherapy
MRC: Medical Research Council
NASS: North American Spine Society
NDI: Neck Disability Index
NMAR: Not missing at random
NPRS: Numerical Pain Rating Scale
PI: Principal investigator
PPT: Pressure Pain Threshold
RCSI: Royal College of Surgeons in Ireland
RCT: Randomised controlled trial
ULNT: Upper Limb Neurodynamic Test
WHO: World Health Organisation
